
### Data analysis

Non-identifying patient information obtained from the standardized case report forms used to collect patient information at baseline, administrative records and medical chart reviews were entered into a Statistical Package for Social Sciences database. All statistical analyses will be performed using IBM SPSS Statistics for Windows, version 20.0 [75]. Descriptive analysis will include demographic details of patients pre-surgery and clinical information collected at the time of surgery. In each analysis to be conducted to address the six main research objectives for this program, categorical variables (such as 30-day complication rate and mortality; and long-term complications e.g., gastro esophageal reflux, micronutrient deficiencies) will be presented as frequencies and chi-square tests conducted to identify differences in pre–post surgical outcomes. Continuous variables with a normal distribution will be reported as means ± SD. Variables with a non-normal distribution will be reported as medians and interquartile ranges. For example, health services use such as number of physician visits often has a non‐normal distribution; therefore median and quartiles will be reported when comparing use pre‐ and post‐surgery. The Analysis of Variance (ANOVA) or the paired t-method will be used to assess differences in continuous outcome pre and post-surgery. Pairwise-comparison of pre with post-surgical patients’ outcomes at 3, 6, 12, 18 and 24 months will be done using matched t-tests for continuous outcomes such as BMI. Regression analyses methods will be performed to identify independent predictors of outcomes of interest (i.e., reduction in weight and/or BMI, including predictors of successful weight loss; improvement or resolution of co‐morbid conditions (i.e., diabetes, hypertension, dyslipidemia, NAFLD, PCOS); changes in prescription and over-the-counter medication use; improvement in measures of health‐related quality of life. For continues outcomes, mean differences, standard errors, 95 % confidence intervals and p-values will be presented. For categorical outcomes, odds ratios and 95 % confidence intervals will be presented. Generalized estimating equations with binary logistic regression will be used for all response or outcome events to take into account the correlations between repeated measures post-surgery providing an estimated adjusted odds ratio and 95 % confidence intervals. Statistical significance is set at *p* < 0.05.

To examine the predictors of change in patient’s 2 years post-surgery, MIXED modelling regression approach [76, 77] implemented in SPSS will be used to assess baseline patient’s factors that determine individual changes in individual maintaining weight loss over the 24 months. The mixed modeling approach will also allow us to take into account the correlations between repeated measures and accounts for missing data over time. Statistical significance effect of factors producing changes or reduction in weight and/or BMI, including predictors of successful weight loss overtime in the 24 month post-surgery would be set at *p* < 0.05. Cost-effectiveness will be performed to evaluate the economic consequences associated with LSG. The economic analyses will be carried out on a per protocol basis and would be based on patients for whom there was complete resource use and health outcome data provided by the NL Centre for Health Information.

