### Complications

Data on complications suggest the benefits of bariatric surgery outweigh the harms [26, 27]. Perioperative mortality is low (<0.3 %) and declining [38]. The incidence of complications (e.g., pulmonary complications, vomiting, wound infection, hemorrhage, anastomotic leak) in the first 30–180 days after surgery varies widely from 4 to 25 % and depends on the definition of complication used, type of procedure, duration of follow-up, and individual patient characteristics. A study by Hutter et al. [39] reviewed the complication rates of 22,365 cases (944 LSG, 14,491 LRYGB, 988 open RYGB, 12,193 LAGB) and found that LSG fell below LRYGB but above LAGB for post-operative rates of morbidity, mortality, readmission, and reoperation rates. Long-term, the rates of reoperation as a result of complications, insufficient weight loss, or weight regain are a concern [40]. The effect of LSG on acid reflux is still controversial and requires further research [41]. Longer term there is some evidence that nutritional deficiencies (e.g., calcium, vitamin D, iron, zinc) may develop after bariatric surgery and the effect on bone health is unknown and also requires further study [26].

Emerging data from observational studies suggest that some bariatric procedures may increase the risk of substance misuse disorders (i.e., alcohol) and suicide [42]. Pharmacokinetic studies suggest that changes in the gastrointestinal anatomy after gastric bypass and sleeve gastrectomy may lead to a more rapid absorption of alcohol and increases in blood alcohol concentrations per dose, inadvertently increasing the frequency of physiological binges and subsequent alcohol misuse disorder [42, 43]. The risk of suicide after bariatric surgery may be increased but the cause is unclear [42]. The Utah Mortality study among others has demonstrated a small but significant increase in the number of suicides after surgery [29]. In addition, there are anecdotal reports of the development of addictive behaviors such as gambling, shoplifting, and driven sexual behavior [43]. It should be noted that these observations are limited due to the paucity of data on long-term psychological assessment in these patients.

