### Study measures

Standardized case report forms (SCRFs) developed in collaboration with Eastern Health and in consultation with other Canadian bariatric programs are used to collect relevant research and clinical data. Clinical data such as weight measures and blood work are collected by the clinical team (the nurse practitioner) and provided to the research team via a research nurse. The research nurse collects data on individual patients at each follow‐up visit using the SCRFs (Table 1).

**Table 1 Tab1:** Study measures and data collection time periods

Study Measures	Source	Variable	Time frame (s)
Socio-demographics/Lifestyle	Patient Interview	Age, sex, ethnicity, current marital status, highest level of education, occupation, current employment status, current household income level, smoking status (current, past, never)	Pre-surgery
Anthropometric	Standardized Case Report Form	Weight^1^, height^2^, BMI^3^	Pre-surgery, 3, 6, 12, 18, 24 months and annually thereafter
Medical History/Self-reported baseline comorbid conditions	Standardized Case Report Form	Diabetes, hypertension, dyslipidemia, sleep apnea, NAFLD, PCOS, etc.	Pre-surgery
Assessment of obesity-related comorbid conditions to evaluate changes in comorbid status	Standardized Case Report Form Patient Interview	Diabetes, hypertension, dyslipidemia, NAFLD, PCOS	3, 6, 12, 18, 24 months and annually thereafter PCOS will be assessed at 12 months only
Medication use	Standardized Case Report Form	Prescribed and over-the-counter medications (name, type, dosage, frequency and duration)	Pre-surgery, 3, 6, 12, 18, 24 months and annually thereafter
Clinical characteristics	Standardized Case Report Form	Blood pressure^4^, heart rate	Pre-surgery, 3, 6, 12, 18, 24 months and annually thereafter
Laboratory values	Meditech laboratory module	HbA1c, fasting blood glucose, insulin level, creatinine, fasting lipid panel (including total cholesterol, LDL, HDL, triglycerides), high sensitivity (hs) CRP, GGT, albumin, total bilirubin, ALP, ALT, total protein, ferritin, hemoglobin, MCV, TSH, 25-OH D, Vitamin B12	Pre-surgery, 3, 6, 12, 18, 24 months and annually thereafter
Health-related QoL	Validated surveys	SF 12v2, EQ‐5D, IWQoL‐Lite	Pre-surgery, 6, 12, 18, 24 months
Operative data	Clinical database and chart review	Minor and major complications	During surgery and up to 30 days post-surgery

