#### Secondary outcomes

Complications of surgery30-day complication rate and mortality will be reported. Longer-term complications such as gastroesophageal reflux and micronutrient deficiencies will be examined. To examine micronutrient deficiencies, the following biochemical parameters associated with micronutrients will be assessed (25-hydroxyvitamin D (25-OH-D), parathyroid hormone (PTH), calcium, vitamin B12, ferritin, mean cell volume (MCV) and hemoglobin). The analysis for 25-OH-D used liquid chromatography coupled with tandem mass spectrometry. Hemoglobin and MCV were analyzed on the Beckman Coulter®HMX Hematology Analyzer, while ferritin, vitamin B12, and intact PTH were analyzed on the Architect i System by Abbots Diagnostics. Calcium was analyzed on the Architect c System by Abbots Diagnostics.Comorbid Condition Improvement/ResolutionImprovement in comorbid conditions (i.e. hypertension and dyslipidemia) is defined as any reduction in medication use or treatment. Comorbidity resolution is defined as complete cessation of treatment/medication.For the comorbid conditions of prediabetes and type 2 diabetes mellitus, specific definitions of diagnosis are used as outlined in the Canadian Diabetes Association Clinical Practice Guidelines [66]. Prediabetes is defined as fasting plasma glucose (FPG) levels of 6.1–6.9 mmol/L and/or glycated hemoglobin (A1C) levels of 6.0–6.4 % [66]. Type 2 diabetes mellitus is defined as FPG ≥ 7.0 mmol/L and/or A1C ≥ 6.5 % [66].Additional criteria will used to assess improvement and resolution of prediabetes and diabetes [67]. Case definitions of improvement and remission of prediabetes will be as follows: *Improvement* will be based on achievement of the following: (1) lower glycemic measures (2) at least 1 year’s duration, and (3) pharmacologic therapy required but at a lower dose. *Normalization* is defined as (1) normal glycemic measures (2) at least 1 year’s duration, and (3) pharmacologic therapy required but at a lower dose. *Remission* is based on (1) normal glycemic measures (2) at least 1 year’s duration, and (3) no active pharmacologic therapy. Case definitions of improvement and remission of Type 2 diabetes mellitus [67] will be defined as follows. *Improvement* will be based (1) hyperglycemia below diagnostic thresholds for T2DM (2) at least 1 year’s duration, and (3) pharmacologic therapy required but at a lower dose. *Partial remission* is based on the following (1) hyperglycemia below diagnostic thresholds for T2DM (2) at least 1 year’s duration, and (3) no active pharmacologic therapy. *Complete remission* is based on the following criteria (1) normal glycemic measures (2) at least 1 year’s duration, and (3) no active pharmacologic therapy.The status of specific biochemical parameters associated with NAFLD prior to and following LSG will be assessed using the following markers: total bilirubin, alanine phosphatase (ALP), alanine transaminase (ALT), gamma glutamyl transpeptidase (GGT), high-density lipoprotein (HDL), low-density lipoprotein (LDL), and triglycerides. Biochemical parameters associated with NAFLD were analyzed on the Architect c System by Abbots Diagnostics.The prevalence of PCOS will be determined prior to surgery based on self-report while changes in related (e.g., period frequency and regularity, menstrual flow and intensity, hirsutism, acne, fertility, post-surgery conception) and metabolic symptoms (insulin sensitivity, T2DM, dyslipidemia, hypertension) will be examined 1-year after LSG.Change in medication useChanges in prescription and over-the-counter medication use and associated costs will be examined including total number of medications and changes (dose changes, medication discontinuations, and initiation of additional medications) by disease indication.Quality of LifeHealth related quality of life is assessed using validated instruments. Generic and disease-specific instruments will be used. All participants will complete the Short Form (SF)-12, Euroqol (EQ)-5D, and the Impact of Weight on Quality of Life (IWQOL)-Lite pre-surgery at 6, 12, 18, and 24 months after surgery. The SF-12 (Version 2) is a condensed 12-question version of the SF-36 [68]. It yields a physical and a mental health component summary score. Three-to-five point difference in either score are considered clinically meaningful [69, 70]. The EQ-5D is an indirect preference-based health survey that consists of a 5 dimension descriptive system [71] and an overall health visual analog scale (EQ- VAS). A 0.03 point difference in EQ-5D index score and 10 point difference on the EQ-VAS are considered clinically meaningful [72]. The IWQOL-Lite is a short form of the IWQOL and is the first instrument specifically developed to assess the effects of obesity on the quality of life of persons who are seeking weight loss treatment [73]. The IWQOL-lite consists of 31 items that describe 5 domains of obesity-specific HRQL. A difference in the total score of 7–12 points for IWQOL-Lite is considered clinically meaningful [74].Economic consequences of bariatric surgeryDirect healthcare use/costs (e.g., hospitalizations, physician visits, medication use) and indirect costs (e.g., cost of weight loss interventions, employment and absenteeism, home productivity, transfer payments) will be compared 3 years prior to surgery and 2 years post- surgery in order to determine the economic consequences of bariatric surgery.

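### The stated pre-post comparison of micronutrient deficiency measures net change, so it can mask deficiency that begins after surgery if pre-surgery deficiency is common and often corrected

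*Protocol article*

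**What the plan says.** Under Secondary outcomes, deficiency is listed with the complications of surgery: "Longer-term complications such as gastroesophageal reflux and micronutrient deficiencies will be examined". The markers named there are 25-OH-D, PTH, calcium, vitamin B12, ferritin, MCV and hemoglobin. The Background section on complications describes the concern as something that arises after the operation: "Longer term there is some evidence that nutritional deficiencies (e.g., calcium, vitamin D, iron, zinc) may develop after bariatric surgery".

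The Data analysis section names the method for this outcome: "micronutrient deficiencies) will be presented as frequencies and chi-square tests conducted to identify differences" in outcomes before and after surgery. Two other statements in that section could touch the same markers:

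- For binary outcomes: "Generalized estimating equations with binary logistic regression will be used for all response or outcome events", the stated purpose being "to take into account the correlations between repeated measures post-surgery".
- For the laboratory values themselves, ANOVA or the "paired t-method will be used to assess differences in continuous outcome pre and post-surgery".

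Table 1 schedules ferritin, hemoglobin, MCV, 25-OH-D and vitamin B12 before surgery, at 3, 6, 12, 18 and 24 months, and yearly after that. Its laboratory row does not list calcium or PTH.

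**The concern.** A complication of surgery is a case that was absent before the operation and present after it. Comparing the frequency of deficiency at two times answers a different question: whether the total number of deficient patients rose or fell. A patient who was already deficient cannot become a new case, but if corrected can offset another patient who became deficient.

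The study hypothesises a low rate of complications, and the abstract counts the effect on nutrition among the complications. If the two flows are of similar size, the stated test reports no change. If correction is the larger flow, it reports an improvement. In either case a reader could not tell how many initially replete patients became deficient. The question is how large this effect could be and under what conditions it arises.

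**Working it through.** **Plan's own figures.** The article gives no numerical target for deficiency. Its only calculation is the sample size for weight loss: 1.2816² × 0.5 × 0.5 / 0.05² = 164.2, rounded up to 165. The total of 200 then implies an allowance of 17.5%, since 165/0.825 = 200. I use N = 200 below. This point does not affect the sample size.

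**Inputs.** Three quantities are needed: p0, the share deficient before surgery; i, new onset among those not deficient; and c, the share of pre-surgery deficiencies that are corrected. The article states none of them, so all values are assumptions.

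**Step 1: what the comparison measures.**

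Post minus pre = (1 − p0) × i − p0 × c

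**Step 2: new onset that leaves the frequency unchanged.** Setting the difference to zero gives i = p0 × c / (1 − p0).

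| p0 | c = 25% | c = 50% | c = 75% |
|---|---|---|---|
| 10% | 0.025/0.90 = 2.8% | 0.05/0.90 = 5.6% | 0.075/0.90 = 8.3% |
| 20% | 0.05/0.80 = 6.3% | 0.10/0.80 = 12.5% | 0.15/0.80 = 18.8% |
| 30% | 0.075/0.70 = 10.7% | 0.15/0.70 = 21.4% | 0.225/0.70 = 32.1% |
| 40% | 0.10/0.60 = 16.7% | 0.20/0.60 = 33.3% | 0.30/0.60 = 50.0% |

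At c = 50% and N = 200 the hidden new cases are 20 of 160, 30 of 140 and 40 of 120 for p0 = 20%, 30% and 40%. At p0 = 0 or c = 0 nothing is offset.

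**Step 3: what the tests return when i = 20% and c = 50%** (N = 200, two-sided, no continuity correction).

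| p0 | Deficient before | New | Corrected | Deficient after | Chi-square p | McNemar p |
|---|---|---|---|---|---|---|
| 0% | 0 | 40 | 0 | 40 | <0.0001 | <0.0001 |
| 10% | 20 | 36 | 10 | 46 | 0.0005 | 0.0001 |
| 20% | 40 | 32 | 20 | 52 | 0.15 | 0.096 |
| 30% | 60 | 28 | 30 | 58 | 0.83 | 0.79 |
| 40% | 80 | 24 | 40 | 64 | 0.096 | 0.046 |

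The last row shows an apparent improvement despite 24 new cases. With 165 patients the pattern is the same: chi-square p = 0.20 at p0 = 20% and 0.84 at p0 = 30%. With i = 20% and no correction, the chi-square test is significant at every p0 tried (p ≤ 0.016).

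**Step 4: exact cancellation.** Take p0 = 30% (60 patients), 28 new cases and 28 corrected. The count is 60/200 before and 60/200 after, so chi-square and McNemar both give p = 1.00. New onset among those at risk is 28/140 = 20% (Wilson 95% CI 14.2% to 27.4%).

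**Step 5: do the other stated analyses help?** The GEE is described for repeated post-surgery measures. It models the odds of being deficient at a visit, which pools persistent and new cases, and no restriction to or adjustment for pre-surgery status is stated for this outcome. The paired comparison of means is also a net change, in which rises in some patients offset falls in others.

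**The case against.** The strongest objection is that the quoted sentence is a generic one. It serves all six objectives and also covers 30-day mortality, which has no pre-surgery value, so for some items frequencies can only mean post-surgery counts. The article condenses a fuller plan, which may contain a table of new cases, and the description of deficiency as something that develops comes from the Background rather than from an outcome definition. All this limits how firmly the sentence can be read, but it does not dispose of the point. Deficiency is named in that sentence, a pre-post test is the method given for it, and the Secondary outcomes section itself lists it as a complication.

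Several stronger readings are tempting and are not supported:

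- *That the pre-post test is the only analysis of deficiency.* The GEE statement covers all outcome events, and the marker values get paired tests. Whether GEE is meant for deficiency is unclear, since the regression outcomes listed just before it omit complications.
- *That new cases will be cancelled, or that the bias must favour the hypothesis.* This needs both appreciable pre-surgery deficiency and substantial correction, and the article reports neither.
- *That replacing chi-square with a paired test would cure it.* McNemar's test also examines the net difference.
- *That correction by supplements can be read from the data.* Table 1 records "Prescribed and over-the-counter medications (name, type, dosage, frequency and duration"; supplements are not named.
- *That every listed marker is already collected.* Calcium and PTH are not in the Table 1 laboratory row.

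It is also fair to object that counting anyone ever deficient would overstate harm, because such a count rises with the number of visits and picks up borderline values. The fix therefore uses status at fixed visits. Some fluctuation around the cut-off will still be counted as new deficiency.

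**Conclusion.** The point holds in a conditional form. The stated comparison estimates new minus corrected cases, and no analysis described in the article isolates new cases. If about 20% or more of patients are deficient before surgery and a substantial share is corrected, the result can be no change or an improvement while roughly 12% to 33% of initially replete patients become deficient (c = 50%, p0 = 20% to 40%). With 20% new onset, the harm would still be detected at a pre-surgery prevalence of 10% or less, or with no correction. Smaller new-onset rates are harder to see: at p0 = 10%, i = 10% and c = 50%, chi-square p = 0.22.

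All these rates are assumptions. The article does not show that masking will happen, only that the stated method cannot rule it out. The point concerns a secondary safety outcome and leaves the primary outcome and sample size untouched. It is worth changing because the correction is cheap and the possible distortion is large.

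**What to change.** In the Data analysis section, keep the pre-post frequencies and add the following for each marker that Table 1 schedules both before surgery and at follow-up (ferritin, vitamin B12, 25-OH-D, hemoglobin and MCV):

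1. The proportion deficient at 12 months and at 24 months among patients not deficient before surgery, with a 95% CI, using the study's own deficiency cut-offs.
2. A table at the same two visits of new, persistent and corrected cases, with the number never deficient and the number without a value.

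Apply the same to calcium and PTH only if pre-surgery values exist, and reconcile the marker list under Secondary outcomes with the Table 1 laboratory row.

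The cost is a sentence or two and one table per marker, with no new data for the five scheduled markers. The denominator is smaller, so intervals widen: at 20% new onset, 14.2% to 27.4% with 140 patients at risk, against 15.0% to 26.1% with 200. Some new cases will reflect borderline fluctuation, which the report should say. The new-onset figure does not show worsening in patients already deficient, so the persistent cases should be shown next to it.

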**Methods:**

A population-based prospective cohort study with pre and post surgical assessments at 1, 3, 6, 12, 18, 24 months and annually thereafter of patients undergoing LSG. This study will report on short - to mid-term (2–4 years) outcomes. Patients (*n* = 200) followed by the Provincial Bariatric Surgery Program between 19 and 70 years of age, with a BMI between 35.0 and 39.9 kg/m^2^ and an obesity-related comorbidity or with a BMI ≥ 40 kg/m^2^ are enrolled. The study is assessing the following outcomes: 1) complications of surgery including impact on nutritional status 2) weight loss/regain 3) improvement/resolution of comorbid conditions and a reduction in prescribed medications 4) patient reported outcomes using validated quality of life tools, and 5) impact of surgery on health services use and costs. We hypothesize a low complication rate, a marked reduction in weight, improvement/resolution of comorbid conditions, a reduction in related medications, improvement in quality of life, and a decrease in direct healthcare use and costs and indirect costs compared to pre-surgery.

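### Pre–post categorical outcomes from the same patients are assigned an ordinary chi-square test, which ignores the pairing; 30-day complications and mortality, listed with them, have no pre-surgery value

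*Protocol article*

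**What the plan says.** The abstract describes the design as "A population-based prospective cohort study with pre and post surgical assessments at 1, 3, 6, 12, 18, 24 months and annually thereafter". There is one cohort and no comparison group, so pre and post values come from the same people.

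In Data analysis, the variables concerned are "categorical variables (such as 30-day complication rate and mortality; and long-term complications e.g., gastro esophageal reflux, micronutrient deficiencies", and the article says they "will be presented as frequencies and chi-square tests conducted to identify differences in" pre- versus post-surgery outcomes. No paired test for categorical data is named.

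The same section does name pairing for continuous data. It offers a paired t-method, and the comparisons at 3, 6, 12, 18 and 24 months "will be done using matched t-tests for continuous outcomes such as BMI".

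It also plans GEE with binary logistic regression for outcome events. The reason given is correlation among the repeated measures after surgery.

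Table 1 (Study measures) gives the time frame for minor and major complications as "During surgery and up to 30 days post-surgery". Secondary outcomes says only that 30-day complications and mortality will be reported.

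**The concern.** The ordinary chi-square test assumes that the two sets of observations are independent. Here each patient contributes to both. A patient who is deficient or has reflux before surgery is more likely than others to have it afterwards, so the two proportions are positively correlated, and the test computes their difference with too large a variance.

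The outcomes exposed are binary and recorded at both times: micronutrient deficiency for markers measured before surgery, a condition or medication present or absent, and reflux if it is recorded at baseline (Table 1 does not name it). Some of these are harms. A test that is too insensitive to a rise in deficiency or reflux errs towards the study's own hypothesis of a low complication rate.

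The 30-day outcomes raise a separate problem. A surgical complication cannot precede the surgery, and every patient is alive at baseline. No pre–post test of these has any meaning, paired or not.

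**Working it through.** **Inputs.** n = 200 (Sample size calculation) and significance at p < 0.05 (Data analysis; taken as two-sided). The article gives no within-patient correlation φ and no prevalence of deficiency or reflux. All values of these below are assumptions, with φ shown from 0 to 0.7.

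**The plan's own figure.** The article gives no figure for the pre–post tests. Its sample size does reproduce: 1.2816² × 0.50 × 0.50 / 0.05² = 164.2, rounded up to 165 (with the printed Z of 1.28: 163.8, or 164). It concerns the 12-month weight-loss proportion and is not at issue.

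**Standard error.** With equal prevalence p at both times:

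- assumed by the ordinary chi-square: variance = 2p(1−p)/n
- true for pairs: variance = 2p(1−p)(1−φ)/n
- ratio of standard errors = 1/√(1−φ)

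**True level of a nominal 0.05 test** = 2 × [1 − Φ(1.96/√(1−φ))].

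| φ (assumed) | SE ratio | True level |
|---|---|---|
| 0 | 1.00 | 0.05 |
| 0.3 | 1.20 | 0.019 |
| 0.5 | 1.41 | 0.006 |
| 0.7 | 1.83 | 0.0003 |

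Neither column depends on n, so loss to follow-up does not change them. A simulation (n = 200, 100,000 replicates, 20% or 50% at both times) agrees: the chi-square rejects in about 2%, 0.6% and 0.04–0.05% of samples at φ = 0.3, 0.5 and 0.7. McNemar's test stays at 4.9–5.2%.

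**Power, same simulation, 20% before and 30% after.**

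| φ (assumed) | Chi-square | McNemar |
|---|---|---|
| 0 | 64% | 64% |
| 0.3 | 67% | 79% |
| 0.5 | 69% | 91% |
| 0.7 | 74% | 99.6% |

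The loss is 12 to 25 points for φ between 0.3 and 0.7.

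**Illustrative table, n = 200.** Deficient both times 40, before only 10, after only 26, neither 124. Before: 50/200 = 25%. After: 66/200 = 33%. Here φ = (40×124 − 10×26)/√(50×150×66×134) = 0.58.

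- Chi-square as two independent groups: pooled proportion 116/400 = 0.29; statistic = 0.08²/(0.29 × 0.71 × 2/200) = 3.11; p = 0.078.
- McNemar: (26−10)²/(26+10) = 7.11; p = 0.008 (exact p = 0.011).
- Paired difference: 8.0 points, SE = √(36 − 16²/200)/200 = 0.0295, 95% CI 2.2 to 13.8 points. The independent-groups SE is √(0.25×0.75/200 + 0.33×0.67/200) = 0.0452, or 1.53 times as large.

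At the article's p < 0.05 the two tests give opposite conclusions.

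**30-day outcomes.** There is no pre-surgery column, so no pre–post calculation exists. An exact binomial 95% interval can be given: 20/200 complications would give 6.2% to 15.0%, and 0/200 deaths would give an upper limit of 1.8%. Both counts are illustrations.

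**The case against.** **The wording may be loose.** McNemar's statistic is referred to a chi-square distribution, so the authors may have meant it. This is possible, but the section spells out pairing for continuous outcomes and omits it for categorical ones. An analyst following the text would run the unpaired test.

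**GEE is already planned for outcome events.** It is, so a correlated-data method is in hand and the remedy is close to a clarification. As stated, though, it addresses correlation among post-surgery measures, and the pre–post contrast is given to the chi-square.

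**The 30-day outcomes may only illustrate variables shown as frequencies.** Table 1 and Secondary outcomes support this, and such a test would probably never be run. The sentence still places them under the pre–post test and should be brought into line. That the article names no interval for them is not a fault in itself, since an article may leave that to the full plan.

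**Stronger readings that a reader might infer, and that the document does not support:**

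- *That false positives will result.* This would require the chi-square to be run on the pre-by-post cross-table, where it tests association rather than change (with 20% at both times and φ = 0.3, it rejects in about 97% of samples). The stated purpose is to identify differences, which points to a comparison of proportions, and there the error is conservative.
- *That every binary secondary outcome is affected.* Improvement, resolution and remission of comorbidities are defined within patient as change and have no separate pre value to test.
- *That confidence intervals are wrong.* The article's intervals for categorical outcomes accompany odds ratios from regression and GEE. None is derived from the chi-square.
- *That the study could not meet its own mortality benchmark.* The background section Complications does say "Perioperative mortality is low", with a figure below 0.3%, but as literature on bariatric surgery. The article sets no mortality threshold.

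**Conclusion.** The point holds for binary secondary outcomes recorded in the same patients before and after surgery. The named test is wrong for such data, and the usual result is p-values that are too large. Its size depends on a correlation the article does not give: there is no loss at φ = 0, and the loss becomes large towards 0.7. The illustrative table shows only that a conclusion can reverse; it does not predict this study's data. Listing 30-day complications and mortality under a pre–post test is a separate error of wording that holds whatever the correlation.

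This should be fixed, but it does not threaten the study. It concerns secondary outcomes, errs on the conservative side and leaves the primary analysis intact.

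**What to change.** In Data analysis:

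1. For each binary outcome recorded before and after surgery, replace the chi-square test with McNemar's test (exact when discordant pairs are few), and report the paired difference in proportions with a 95% confidence interval. Alternatively, state that the pre-surgery record enters the planned GEE logistic model as a time point, and take the pre–post contrast from it.
2. Remove 30-day complications and mortality from the pre–post test. Report them as proportions with exact binomial 95% intervals, in line with Secondary outcomes.
3. State which categorical outcomes have a pre-surgery value. Table 1 does not name reflux, PTH or calcium, so confirm that these are recorded at baseline before planning a pre–post test for them.

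The cost is a sentence or two of text. No new data or patients are needed for outcomes already recorded at both times, and SPSS, the software already named, provides both McNemar's test and GEE.
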